## Abstract

**Background:**

Tobacco and alcohol use present multiplicative risk for aerodigestive cancers. Reducing alcohol consumption improves smoking cessation outcomes and reduces cancer risk. Risky alcohol consumption and smoking are often treated separately despite concurrent treatment potentially leading to better outcomes for each. However, no rapidly scalable program exists for combined interventions in primary care clinics spread across wide geographic areas. This cluster randomized trial aims to report on the effects of a novel clinical decision support system (CDSS) on intervention rates by primary care practitioners addressing risky alcohol use in a smoking cessation program.

**Methods/design:**

We will be implementing a clinical decision support system (CDSS) in 221 primary care sites participating in the Smoking Treatment for Ontario Patients (STOP) program across Ontario, Canada. Sites will be blindly allocated to one of two clinical decision support systems guiding practitioners to provide a risky alcohol use intervention to smokers attempting to quit using nicotine replacement therapy (NRT). Risky alcohol use is defined as drinking above the Canadian Cancer Society’s low-risk drinking guidelines. Primary analysis will measure the proportion of risky drinkers offered an alcohol intervention in each CDSS arm at baseline. Patients will be contacted by phone or email to track smoking cessation and alcohol consumption rates at 6- and 12-month follow-up.

**Discussion:**

Upon completion of the trial, the effect of different clinical decision support systems on practitioner behaviour, and on client tobacco and alcohol use, will be discussed. If the CDSS successfully promotes SBIRT for risky alcohol use in a primary care setting and/or improves patient-level outcomes, including smoking cessation rates and alcohol use reduction, this tool can be used as a model for other web-based behaviour change interventions integrated into primary care practice.

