### Patient screening

Participants in the COMBAT trial will be enrollees of the existing STOP smoking cessation program and will therefore be cigarette smokers wishing to quit, or those who have already begun their quit attempt.

Upon enrollment in the STOP program, participants will complete a baseline enrollment survey about their tobacco use and related measures. Alcohol consumption will be measured on the baseline survey using a seven-day timeline followback (TLFB) questionnaire [37] and the Alcohol Use Disorders Identification Test (AUDIT) [38]. Women consuming seven or more and men consuming fourteen or more alcoholic beverages (13.6 g per standard drink) in the past week—as measured by the TLFB—as well as any individual endorsing any episode of consuming five or more drinks on one occasion (AUDIT item 3) will be considered to be exceeding the Canadian Cancer Society (CCS)’s cancer prevention alcohol consumption guidelines [39]. In order for a participant to be eligible for the COMBAT trial, their baseline enrollment survey must be administered by a practitioner, in English, into the online portal in real time, so that the clinical interaction can be supported by the CDSS. Therefore, those patients who are administered the baseline survey on paper, or in French, cannot be included in the trial.

Patient consent for participation in the STOP smoking cessation program will be obtained at the time of enrollment. Individuals younger than 18 years old will enroll with the consent of their legal guardian if required to do so.

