### Outcomes

The primary outcome of the study, measured at the cluster level, will be the offer of an appropriate educational alcohol resource, reduction or abstention, to patients exceeding the cancer prevention alcohol consumption guidelines upon completion of STOP smoking cessation program enrollment. This dichotomous outcome is recorded by the STOP program’s online portal for each enrolling participant.

Given that patients can refuse practitioners’ offer of resources, the secondary outcome of the study, measured at the cluster level, will be the acceptance of the educational alcohol resource by patients exceeding the cancer prevention alcohol consumption guidelines. This dichotomous outcome is also recorded by the STOP program’s online portal for each enrolling participant.

The tertiary outcome, measured at the patient level, will be patient abstinence from smoking, and alcohol consumption within cancer prevention guidelines, at the 6-month follow-up survey as recorded in the STOP program’s online portal. Smoking abstinence will be defined by a negative response to the seven-day point prevalence question, “Have you had a cigarette, even a puff, in the last 7 days?” Alcohol consumption at follow-up will be measured using the same survey items as those used in the baseline enrollment survey, described previously. Alcohol consumption within CCS guidelines will be defined as the inverse of alcohol consumption in excess of CCS guidelines.

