### Statistical methods and analysis

Descriptive statistics will compare cluster-level and patient-level baseline characteristics between the two treatment groups.

Results will be analyzed using a generalized estimation approach for fitting logistic regression using a population-averaged method with treatment arm and stratification variables (i.e. organization type and cluster size) regarded as fixed effects and clinic (i.e. cluster) as random effects in the model. To account for clustering, an exchangeable correlation matrix and robust standard errors will be specified [45]. The intra-cluster correlation coefficient will be estimated, and if it is found to be negative, an analysis not adjusting for clustering will be used.

The following baseline variables will be treated as potential confounders: gender; age; body mass index; identifying as First Nations, Inuit or Métis; household income; employment status; educational attainment; depression; AUDIT-C score; heaviness of smoking index; marijuana use; opioid use; treatment for mental health problem; drug treatment; and comorbid conditions. To identify the covariates to be included in the statistical models for the primary, secondary and tertiary analyses, we will fit separate models including each covariate one at a time. The final model will include those covariates such that their inclusion changes the estimated treatment effect by at least 10%. Decisions about the inclusion of covariates will not be based on statistical significance (i.e. *p* values).

As the primary and secondary outcomes will be captured by the online portal, complete case analyses will be used (i.e. imputation will not be used for these outcomes). The tertiary outcome will be available only for those patients who complete a 6-month follow-up survey; therefore, missing data is expected. A single imputation of best-case scenario (i.e. not smoking and drinking within guidelines) and a single imputation of worst-case scenario (i.e. smoking and drinking in excess of guidelines) will be conducted. If the best-case and worst-case scenarios imply different conclusions, a multiple imputation approach that accounts for the clustered structure of the data will be employed.

All analyses will follow an intention-to-treat approach in which clusters and participants are analyzed in the intervention arm to which they were originally assigned.

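### The tertiary outcome is worded as one joint smoking-and-drinking state with no baseline level and no named population, so smoking and alcohol may not each get their own answer

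*Protocol article*

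**What the plan says.** The abstract treats smoking and alcohol as two patient results. Its Methods/design paragraph says patients will be contacted to "track smoking cessation and alcohol consumption rates at 6- and 12-month follow-up". Its Discussion says that effects on clients' tobacco and alcohol use will be discussed, and adds a conditional sentence about a tool that "improves patient-level outcomes, including smoking cessation rates and alcohol use reduction". The section Retrospective trial registration describes the tertiary outcome as a measure of behaviour change in patients and gives this as the reason for registering.

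The Outcomes section defines it: "The tertiary outcome, measured at the patient level, will be patient abstinence from smoking, and alcohol consumption within cancer prevention guidelines", at the 6-month survey. On smoking, "Smoking abstinence will be defined by a negative response to the seven-day point prevalence question". On alcohol, the patient must not exceed the guidelines, judged on the same survey items as at enrolment. The primary and secondary outcomes are limited to patients exceeding the guidelines. The tertiary outcome carries no such limit, and the workflow text says all patients are followed up.

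For missing data, Statistical methods and analysis gives a "best-case scenario (i.e. not smoking and drinking within guidelines" and a worst case of smoking and drinking in excess. AUDIT-C and the heaviness of smoking index are only candidate covariates, kept if they move the treatment effect by at least 10%. Patient screening admits "cigarette smokers wishing to quit, or those who have already begun their quit attempt".

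**The concern.** If the tertiary outcome is one yes/no state, a patient succeeds only by meeting both conditions. The decision support acts on drinking, so any effect on smoking is indirect. A real gain in drinking can be hidden behind the many patients who still smoke, and neither behaviour gets its own estimate.

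The alcohol part is also a threshold state at follow-up. A patient who goes from 40 to 20 drinks a week, the kind of change the reduction resource encourages, still exceeds the guidelines and is not credited. The same holds for one who cuts weekly drinking sharply but still reports an episode of five or more drinks.

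On smoking, some patients may already have stopped at enrolment. They can count as abstinent at 6 months without any cessation during the trial, and quit status at entry is not among the listed covariates.

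If two outcomes were intended, the text does not say so, and the choice could be made after data are seen.

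**Working it through.** **The plan's own figures.** None is given for the tertiary outcome. The sample size is for the primary outcome: 23 × 189 = 4347, all exceeding guidelines at baseline. With an intra-cluster correlation of 0.04, a coefficient of variation of 1.04 and a relative-efficiency design effect of 2.576, the detectable relative risks come out at 1.447 (control proportion 0.1) and 1.041 (0.9). These agree with the stated 1.45 and 1.04. They say nothing about the tertiary outcome.

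**One outcome or two?** The singular noun and the joining *and* point to one. The Outcomes section, however, defines each part on its own. The two imputation scenarios are also not complements: failing a joint state means smoking *or* drinking in excess, whereas the worst case is smoking *and* drinking in excess. That fits two outcomes as well as one.

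**Dilution on the joint reading.** All rates here are assumed, since the protocol gives none. The standardised difference is d = (p2 − p1)/√[p̄(1 − p̄)], and the ratio of required sample sizes is (d for alcohol / d for joint)². The design effect is taken as equal for both outcomes, so it cancels.

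- Alcohol alone, 30% v 36%: 0.06/√(0.33 × 0.67) = 0.128.
- Joint, behaviours independent, abstinence 25% in both arms: 0.25 × 0.30 = 0.075 and 0.25 × 0.36 = 0.090, so d = 0.015/√(0.0825 × 0.9175) = 0.0545. Ratio (0.1276/0.0545)² ≈ 5.5.
- Abstinence 25% v 28%: 0.075 v 0.28 × 0.36 = 0.1008, so d = 0.0258/√(0.0879 × 0.9121) = 0.0911. Ratio ≈ 2.0.
- Abstinence 25% v 30%: 0.075 v 0.108, so d = 0.033/√(0.0915 × 0.9085) = 0.1145. Ratio ≈ 1.2.
- Behaviours linked, abstinence 25% in both arms, 20% relative gain in the alcohol part: if 50% of control abstainers drink within guidelines, the joint state is 12.5% v 15.0% and the ratio about 3.1. If 70% do, it is 17.5% v 21.0% and about 2.1.

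**Patients already quitting at entry.** Assume 6-month abstinence of 50% in those already quit and 25% in smokers, with a relative risk of 1.20 in smokers only.

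- 10% already quit: (0.1 × 0.50 + 0.9 × 0.30)/(0.1 × 0.50 + 0.9 × 0.25) = 0.320/0.275 = 1.16.
- 30% already quit: (0.3 × 0.50 + 0.7 × 0.30)/(0.3 × 0.50 + 0.7 × 0.25) = 0.360/0.325 = 1.11.

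**The case against.** The strongest reply is that the protocol's aim is practitioner behaviour: the trial "aims to report on the effects of a novel clinical decision support system (CDSS) on intervention rates by primary care practitioners". The sentence about improving patient outcomes is conditional. The tertiary outcome is last in rank, and the Discussion already doubts its power. This stands and limits the weight of the point. It does not remove it, because the abstract and the registration section also promise results on patient smoking, alcohol and behaviour change without condition.

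A reader might infer three stronger things that the document does not support.

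- *That the outcome cannot show reduction at all.* Among patients above the guidelines at baseline, being within them at 6 months is itself a reduction, and randomised arms can be compared on it without a baseline value. Only reductions that stay above the threshold are missed. The same items are asked at both times, so change can still be derived.
- *That patients who had already quit bias the result.* The text speaks of a quit attempt already begun, which is not the same as abstinence, and gives no proportion. Such patients are expected in both arms. They may dilute the effect and blur what cessation means, but they do not bias the comparison.
- *That weekly drinks should replace the guideline state.* Exceeding guidelines also covers any episode of five or more drinks, and a patient can qualify on that alone. Replacing the state would lose that criterion. For the same reason, and because weekly drinks are likely to be skewed, I put no figure on the information lost by using the threshold.

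**Conclusion.** The point holds as a fault of definition. The Outcomes section does not settle whether the tertiary outcome is one state or two, does not name its population, and uses no baseline level in its definition. On the likely joint reading, an effect on drinking cannot be told apart from one on smoking.

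The size of the dilution depends on assumptions. It is about 5.5-fold in required patients if the behaviours are independent and abstinence is 25% in both arms. It is about 2-fold if abstinence also rises to 28%, about 1.2-fold at 30%, and about 2- to 3-fold if abstainers are more likely to drink within guidelines. The 5.5 is therefore the least favourable of the scenarios tried, not an estimate for this trial.

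The primary and secondary outcomes are untouched. As this is a tertiary outcome without planned power, the matter is of minor to moderate weight, but it is cheap to put right.

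**What to change.** In Outcomes, define two separate tertiary outcomes in patients exceeding the guidelines at baseline:

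- (a) 7-day smoking abstinence at 6 months, adjusted for smoking or quit status at enrolment where the baseline survey records it;
- (b) drinking within guidelines at 6 months, keeping the criterion of an episode of five or more drinks.

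Add weekly drinks from the 7-day timeline followback at 6 months, adjusted for the baseline value in a model suited to a skewed count, as a supporting alcohol result. Keep the joint state as descriptive.

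In Statistical methods and analysis, apply the best-case and worst-case imputation to each behaviour separately. Include the baseline value of each outcome whatever the 10% change rule says, since that rule can drop a strongly prognostic variable that happens to be balanced between arms.

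The alcohol items are already collected at both times, so the cost is wording and a few models. The downside is several tertiary estimates instead of one, in an area already disclosed as possibly underpowered.

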**Trial registration:**

ClinicalTrials.gov NCT03108144

## Background

In the coming decades cancer is set to become a major cause of morbidity and mortality in every region of the world [1]. The evidence indicates that both tobacco use and alcohol consumption are independently major preventable risk factors [2]. Tobacco use increases the risk of developing at least 14 types of cancer and accounts for about 25–30% of all deaths from cancer, including 87% of deaths from lung cancer [2]. Alcohol consumption is causally related to cancers of the oral cavity, pharynx, larynx, oesophagus, liver, colon, rectum, and female breast [3]. Alcohol use accounts for about 3 and 10% of total cancers diagnosed in women and men, respectively, and of that, 40–98% occurs due to alcohol consumption greater than the recommended guidelines [4, 5]. Furthermore, the combined use of alcohol and tobacco confers a multiplicative, positively associated risk for aerodigestive and other related cancers [6–14]. For example, the combined effect of tobacco and alcohol has been shown to produce a population-attributable risk (PAR) of 85% for hypopharyngeal/laryngeal cancer, demonstrating that 85% of cases would be eliminated if concurrent alcohol consumption and smoking had never occurred [15]. Similarly, co-use of alcohol and tobacco explains a large proportion of oropharyngeal (PAR = 74%), esophageal (PAR = 67%), and oral cancers (PAR = 61%) [15].

There is substantial high-quality evidence that shows the efficacy of Screening, Brief Intervention, and Referral to Treatment (SBIRT) to reduce hazardous drinking [16–23]. However, few health care practitioners have implemented brief alcohol interventions into their daily routine despite the short time commitment (5–10 min) [24]. Furthermore, excess alcohol consumption and smoking are often treated separately; although, reducing or stopping drinking when quitting smoking and vice versa may lead to better outcomes [25–28]. With a lack of clear pathways, health care practitioners may be less likely to address alcohol consumption in smoking cessation treatments, thus presenting a missed opportunity for cancer prevention.

There is potential to address this gap through implementation of just-in-time clinical decision support systems (CDSSs). A CDSS is an interactive computer program designed to assist health care practitioners by automating simple decision-making processes enabling efficiency in the workplace to improve patient care [29–33].

This study aims to assess whether the addition of a web-based CDSS—designed to prompt practitioners in real time to conduct SBIRT with patients who are drinking above recommended guidelines—influences the proportion of practitioners delivering a brief intervention to their eligible patients quitting smoking.

In this paper, we describe the protocol for a cluster randomized trial named “Personalized patient alerts and care pathways to prompt prevention interventions for combined alcohol and tobacco users in primary care” or COMBAT. The COMBAT trial will be operationalized via the Smoking Treatment for Ontario Patients (STOP) program, an established smoking cessation program implemented at the primary care level in Ontario, Canada. The STOP program offers up to 26 weeks of smoking cessation treatment, consisting of nicotine replacement therapy and behavioural counseling, at no cost to the patient.

## Methods/design

### Participants

Primary health care clinics in Ontario, Canada, implementing an existing smoking cessation program—the STOP program—at the time of the study are eligible to participate. The vast majority of three types of primary health care clinics across Ontario implement the STOP program: 150 out of 184 family health teams (FHTs), 59 out of 67 community health centres (CHCs), and 17 out of 23 nurse practitioner-led clinics (NPLCs). Clinics enroll their patients into the STOP program using a centralized, online portal; the STOP portal is an online data management and collection tool used by all clinics to complete participant enrollment, record smoking status at each visit, monitor treatment, and receive real-time progress reports. This tool allows for processes to be streamlined and for health care practitioners to track their patients’ progress throughout the program. All those FHTs, CHCs and NPLCs operational in the STOP program as of March 14, 2016 (222 clinics), are eligible for randomization, except one known to use paper-based patient enrollment options exclusively (i.e. any clinic not using the online portal). In total, 221 clinics will be randomized into the COMBAT trial.

To build capacity of all practitioners implementing the STOP program, an interactive webinar will be presented on SBIRT implementation using CDSS, as web-based SBIRT training has shown to be effective for and favourable among primary care practitioners [34]. The webinar audience will include the STOP Community of Practice (*n* = 300) of implementers, physicians, and executive directors, who interact through bi-weekly teleconferences to communicate updates, clarify procedures, address barriers or gaps in program delivery, and share experiences with other practitioners.

### Trial design

The COMBAT study will be a cluster randomized controlled trial with clusters (i.e. primary care clinics in Ontario, Canada) randomized to one of two treatment arms. Health care practitioners working in clinics randomized to the intervention arm, group B, will receive computer alerts when a patient is identified as consuming alcohol above the recommended guidelines and will be guided to provide the patient with a brief intervention and an educational workbook. Practices randomized to the treatment-as-usual arm, group A, will have access to the same resources available to practitioners in group B but will not receive computer alerts.

The web-based CDSS will take advantage of a platform that overcomes the common barriers to system-wide implementation, such as expensive time-consuming programming changes and validation for each electronic medical record (EMR) system, and will have features that are associated with improvement, such as clinical workflow integration, decision support at time of care, and electronic and direct recommendations [35].

### Randomization

Clinics will be the unit of randomization. Two stratification factors will be defined: clinic type with three levels (FHT, CHC, and NPLC) and clinic size with two levels, resulting in six strata. Actual clinic size, measured as number of trial participants enrolled, is not directly observable a priori; therefore, expected clinic size will be estimated based on past STOP enrollment. Independently for each clinic type, the two levels of clinic size will be set such that expected total enrollment in the two levels will be balanced. Within each stratum, clinics will be randomly allocated in a 1:1 allocation ratio to control (group A) or intervention (group B). Treatment allocation (randomization) for each clinic will be determined for all operational clinics en masse. Any clinics that begin implementing the STOP program after the randomization cut-off date (April 11, 2016) will not be eligible for participation in the COMBAT trial. The random assignment of treatment to clinic will be computer generated using the ralloc command of statistical computer software Stata V.13 [36].

### Blinding

This pragmatic, cluster trial is designed to evaluate an intervention to change practitioners’ behaviour. Blinding of the clinic via its practitioners will therefore not be possible as the practitioner will be aware of the presence or absence of the portal prompting system.

Participating clinics will not be told of their treatment allocation until the trial begins. Investigators are blinded to the randomization arm. Data analysis will be blinded to treatment allocation.

